### Criteria for randomization and blinding

3.4

Stratified block randomization will be used, stratified by Stanford type (A or B). Random sequences were generated using SAS 9.4 software and concealed in sequentially numbered, opaque, sealed envelopes, which will be managed by an independent statistician.

A single-blind design (participant-blinded) is employed to minimize participant bias in self-reported outcomes (e.g., pain or bloating scores). The stimulation devices for both groups are identical in appearance. Each device has pre-programmed “active” and “sham” stimulation modes, which can only be toggled by a device engineer using a hidden password. In sham mode, the device displays identical operation indicators and parameter values as in active mode, but without any current output, thus preventing physiological effects and maintaining blinding. Outcome assessors for psychological scales (e.g., HAMA, HAMD, and GIDS) will be blinded to group assignment and not involved in intervention delivery. They will only receive de-identified subject IDs and corresponding raw scale data. Similarly, all samples for gut microbiota, serum biomarkers, and brain function analyses will be de-identified. Laboratory personnel will submit results linked only to sample codes, and the final linkage of codes to group assignment will be performed by the independent statistician.

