#### Data collation

3.9.1

Data will be collected using CRFs, capturing baseline characteristics, intervention records, laboratory results, and scale scores. All biological specimens will be de-identified via unique codes to protect participant privacy. Statistical analyses will be performed using SPSS 22.0, with the following approach:

① Statistical Tests by Data Type: Categorical variables will be summarized as frequencies (percentages) and compared using the chi-square test. Continuous variables will be presented as mean ± standard deviation; after testing for normality and homogeneity of variance, parametric data will be analyzed using *t*-tests (independent or paired, as appropriate), while non-parametric data will be analyzed using the Mann–Whitney *U* test (rank-sum test). Ordinal data (e.g., scale scores) will also be analyzed using non-parametric rank-sum tests.

② Analysis of Primary and Secondary Outcomes: Outcomes include scale scores (GIDS, HAMA, HAMD, SF-36, and PSQI), brain function parameters (EEG, fNIRS-derived rCBF), gut microbiota metrics (diversity indices, taxon abundance), and biochemical markers (IL-6, TNF-α, 5-HT, and BDNF). A stratified multiple comparison adjustment will be applied: the primary outcome will use Bonferroni correction (corrected α = 0.01, accounting for five indicators), while secondary outcomes and biomarkers will use the False Discovery Rate (FDR) method (FDR = 0.05). Subgroup analyses (e.g., by gender, Stanford type) will also employ FDR correction to control Type I error inflation.

③ Correlation Analysis: Multiple linear regression will be used to explore associations between clinical outcomes, gut microbiota, inflammatory markers, and brain function.

④ Significance Level: A two-sided *P* value < 0.05 will be considered statistically significant for all tests, unless otherwise specified after multiplicity adjustment.

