#### Main statistical models

3.9.2

Mixed-effects models will serve as the core analytical framework to handle repeated measures collected at 1 day, 7 days, 4 weeks, and 24 weeks postoperatively. ① A linear mixed-effects model will be used for continuous outcomes, including gut microbiota indices (Shannon index, Bifidobacterium abundance), brain function parameters (fNIRS rCBF, EEG α-wave power), and biochemical markers (IL-6, TNF-α, 5-HT, and BDNF). ② A logistic mixed-effects model will be applied to binary outcomes, such as adverse events (SAE, skin allergy) and intestinal function recovery (first flatus within 48 h, first defecation within 72 h). ③ An ordinal logistic mixed-effects model will be used for ordinal outcomes, including scale scores (GIDS, HAMA, and HAMD).

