
The innovations of this study are reflected in three aspects: First, the combination of taVNS and the GBA theory is applied to the postoperative management of AD for the first time, overcoming the limitations of traditional single-system interventions by regulating complications through the synergistic actions of neural, immune, and endocrine pathways. Second, a multidimensional outcome indicator system is utilized, which includes not only core GBA biomarkers such as gut microbiota diversity and inflammatory factors but also, through collaboration with the rehabilitation department, real-time monitoring of brain function changes via BCI and fNIRS, enabling cross-system correlation analysis of intestinal function, inflammation, and brain function in postoperative patients. Third, a randomized controlled design is strictly followed: a sham stimulation control (with no current output, targeting non-vagus nerve innervated areas) is implemented, and stratified randomization based on the Stanford classification is employed to reduce bias and enhance the reliability of the results.

From a methodological perspective, the intervention protocol in this study is rigorously designed. For taVNS, the stimulation sites are selected as the cymba conchae or tragus (areas rich in the auricular branches of the vagus nerve), and the parameters are set to a frequency of 15 Hz and a pulse width of 200 μs—based on international standards and previous anti-inflammatory research evidence—to ensure the stimulation intensity is within patients' tolerance range while effectively activating the vagus nerve pathway. The sample size estimation is based on effect sizes of gut microbiota and inflammatory factor changes reported in similar studies; after accounting for a 10% dropout rate, 25 cases per group were determined, meeting statistical power requirements. The procedures for collecting and processing biological specimens (e.g., fecal samples stored at −80 °C, metagenomic sequencing for gut microbiota structure analysis) are standardized, and analyses are conducted by third-party laboratories to ensure data objectivity.

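### Sections 3.9.1 and 3.9.2 prescribe different tests for the same outcomes without saying which decides, and the use of Stanford type and the day-1 value in the deciding analysis is not stated

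*Protocol article*

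**What the plan says.** Section 3.4 sets the allocation: "Stratified block randomization will be used, stratified by Stanford type (A or B"). The Discussion gives the purpose: "stratified randomization based on the Stanford classification is employed to reduce bias".

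Section 3.9.1, item ①, chooses tests by data type. For continuous variables, "after testing for normality and homogeneity of variance, parametric data will be analyzed using" t-tests, independent or paired, with Mann–Whitney as the non-parametric alternative. For scales, "Ordinal data (e.g., scale scores) will also be analyzed using non-parametric rank-sum tests". Categorical variables get a chi-square test.

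Section 3.9.1, item ②, sets the multiplicity rule: Bonferroni with α = 0.01 for the primary outcome (five indicators) and FDR at 0.05 for the rest. Here Stanford type makes its only appearance in the analysis section: "Subgroup analyses (e.g., by gender, Stanford type) will also employ FDR correction".

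Section 3.9.2 then states that "Mixed-effects models will serve as the core analytical framework", for measurements at day 1, day 7, week 4 and week 24. "A linear mixed-effects model will be used for continuous outcomes, including gut microbiota indices", brain-function parameters and biochemical markers. For scales, "An ordinal logistic mixed-effects model will be used for ordinal outcomes, including scale scores (GIDS, HAMA, and HAMD"). No fixed effects or covariates are listed.

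Table 1 places Visit 2 on postoperative day 1, before the intervention.

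**The concern.** Two sections each prescribe an inferential method for the same hypotheses. If a t-test and a mixed model disagree on the Shannon index, or a rank-sum test and an ordinal mixed model disagree on HAMA, the text does not settle which result is the trial's result. The choice could then be made after the data are seen. The multiplicity rule does not prevent this, because it is tied to neither method.

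The second matter is precision. A factor used to balance the allocation is normally carried into the analysis. If it is prognostic and left out, the standard error is too large for the balance achieved. The same economy applies to the pre-intervention value. With 25 patients per arm, either loss matters.

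**Working it through.** **1. The two sections side by side**

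| Outcome | Section 3.9.1 | Section 3.9.2 |
|---|---|---|
| Microbiota indices, fNIRS/EEG parameters, IL-6, TNF-α, 5-HT, BDNF | t-test or Mann–Whitney | linear mixed model |
| GIDS, HAMA, HAMD | rank-sum | ordinal logistic mixed model |
| Stanford type | subgroup analyses only; the tests carry no covariate | not mentioned; no fixed effects listed |
| Day-1 (pre-intervention) value | no adjustment in the between-group tests | one of the repeated measures; role not stated |
| Which result decides | not stated | called core; not stated to be the only deciding analysis |

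**2. Inputs for the size of the loss**

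From section 3.3: difference 3, SD 5, so d = 3/5 = 0.6; 25 per arm randomised; two-sided α = 0.05. From section 3.9.1: corrected α = 0.01. The article gives neither the baseline–follow-up correlation r nor the share of variance explained by Stanford type, so both are assumed over a range.

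The plan states no power figure for this point. Its nearest figure is the 22 per group in section 3.3. The standard formula gives 2 × [(1.96 + 0.84) × 5/3]² = 43.6, so 44 per group. The stated 22 follows only if the leading factor 2 is dropped (21.8). That is a separate matter, but it explains why the powers below start well under 80%.

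**3. Baseline handling** (25 per arm, noncentral t with 48 df)

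- Follow-up-only t-test: d = 0.6.
- Unadjusted change score: d = 0.6/√[2(1 − r)], giving 0.507, 0.600 and 0.775 for r = 0.3, 0.5 and 0.7.
- Baseline-adjusted: d = 0.6/√(1 − r²), giving 0.629, 0.693 and 0.840.

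| Power | r = 0.3 | r = 0.5 | r = 0.7 |
|---|---|---|---|
| α = 0.05, follow-up only | 55% | 55% | 55% |
| α = 0.05, change score | 42% | 55% | 77% |
| α = 0.05, baseline-adjusted | 59% | 67% | 83% |
| α = 0.01, follow-up only | 30% | 30% | 30% |
| α = 0.01, change score | 20% | 30% | 53% |
| α = 0.01, baseline-adjusted | 33% | 42% | 61% |

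With complete data, the change-score row is what a mixed model's treatment-by-visit contrast delivers when the day-1 means are left free in each arm. The adjusted row approximates what it delivers when day 1 is a covariate or its means are constrained equal.

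**4. Stanford type** (simulation: 40,000 runs, 22 per arm, half in each stratum, total SD 5, α = 0.05)

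| Variance explained (assumed) | Unadjusted type I error | Unadjusted power | Adjusted power |
|---|---|---|---|
| 0% | 4.9% | 49% | 49% |
| 10% | 3.7% | 49% | 54% |
| 20% | 2.6% | 49% | 58% |
| 30% | 2.0% | 49% | 64% |

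The adjusted model's type I error stays near 5% throughout. The unadjusted test is conservative and gives up roughly 4 to 15 points of power when the stratum explains 10–30% of the variance.

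**The case against.** The strongest reply is that the text already implies a hierarchy. Section 3.9.2 is headed as the main models and calls them core, while section 3.9.1 sits under data collation and lists generic tests by data type. That is fair as a hint of priority. But 3.9.1 says these tests will be used, attaches the multiplicity rule to no method, and never calls the tests supportive. The overlap also reaches the primary microbiota and brain-function outcomes, not only the secondary scales.

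A second reply is that a condensed article may leave model covariates to the full protocol or SAP. This stands for the mixed models. A reader might infer that no analysis adjusts for Stanford type, but 3.9.2 lists no fixed effects at all, not even treatment, so the absence is silence and not evidence of non-adjustment. Only the 3.9.1 tests, as named, leave the stratum out.

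A reader might likewise infer that the day-1 value goes unused. The documents contradict that: day 1 is among the mixed model's time points, and Table 1 defines it as before the intervention. What is open is whether it enters as a free response, a constrained response or a covariate.

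Finally, 3.9.1 permits paired t-tests where appropriate. It does not name within-arm change as evidence of efficacy, so predicting that such tests will be significant in both arms goes beyond the text.

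**Conclusion.** The point holds in this form: two sections fix different methods for the same outcomes, the deciding result is not identified, and the use of Stanford type and of day 1 in the deciding analysis is not stated. The consequences are a free choice between analyses and avoidable loss of precision.

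It would be wrong to infer that either single analysis has an inflated error rate. Leaving out a prognostic stratum makes the unadjusted test conservative.

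The power figures illustrate what is at stake and do not describe the planned core analysis, whose contrast is unknown. They rest on d = 0.6 from section 3.3, all 25 patients per arm being analysed, and assumed correlations of 0.3 to 0.7. At r = 0.3 a change-score contrast (42%) does worse than ignoring baseline (55%), and at r = 0.7 it is close to full adjustment (77% against 83%). The Stanford figures rest on an assumed 10–30% of variance explained, equal strata and 22 per arm. This should be changed, but it does not invalidate the trial.

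**What to change.** - State that the mixed model is the only confirmatory analysis and that the Bonferroni and FDR rules apply to its P values.
- List its fixed effects: treatment, visit, treatment-by-visit and Stanford type.
- State how Visit 2 is handled. Either make it a covariate and remove day 1 from the responses listed in 3.9.2, or keep it as a response with baseline means constrained equal across arms.
- Name the one between-group contrast that decides, including the visit. Which visit is the sponsor's choice; the article does not fix it.
- Make the 3.9.1 tests, including any paired within-arm tests, descriptive or supportive only.

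The cost is analysis wording, settled before any outcome is seen by group. Stanford type and the day-1 value are already collected, so no visit, sample or patient is added.

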### Intervention

3.5

#### Intervention group

3.5.1

Participants will receive conventional postoperative basic care for AD (e.g., blood pressure control, anti-infection therapy, and nutritional support) combined with taVNS: ① Stimulation sites: Bilateral tragus or cymba conchae, corresponding to the international standardized auricular points CO10 (“Shenmen”) and CO15 (“Cymba Conchae”), which are densely innervated by the auricular branch of the vagus nerve. ② Frequency = 15 Hz; pulse width = 200 μs; current intensity will be individually titrated from 1 mA to a perceptible yet non-painful level (maximum ≤ 5 mA). ③ taVNS stimulators certified by the National Medical Products Administration or the U.S. Food and Drug Administration.

#### Control group

3.5.2

Participants will receive conventional postoperative care for AD (identical to the intervention group) plus sham stimulation: ① Stimulation target: The scaphoid fossa (auricular points SF3, SF5), a non-vagus innervated region. ② Electrode placement: Identical in appearance to the active group (bilateral tragus or cymba conchae) to maintain blinding. ③ Parameters: Frequency, pulse width, and duration match the active taVNS group, but with zero current output.

#### Intervention and follow-up period

3.5.3

All patients will receive standardized postoperative management, including nutritional support (standard liquid/semi-liquid diet) supervised by the hospital nutrition department. Concomitant medications affecting gut microbiota or motility will be documented. ① Intervention frequency: Twice daily, 30 min per session. ② Start time: Postoperative day 1. ③ Intervention course: 7 consecutive days. ④ Follow-up: Participants will be followed for 24 weeks, with periodic assessments of efficacy (e.g., inflammatory markers, gut microbiota, quality of life) and safety (e.g., adverse events, vital signs).

### Outcome measures

3.6

#### Main outcome measures

3.6.1

① Gut Microbiota Diversity and Abundance: Fecal samples will be analyzed using metagenomic sequencing. Key metrics will include the abundance of probiotics (e.g., Bifidobacterium, Lactobacillus)—where reduced abundance reflects gut microbiota imbalance and indicates dysbiosis—the abundance of opportunistic pathogens (e.g., Escherichia coli, Enterococcus)—whose excessive proliferation may disrupt the intestinal barrier and induce systemic inflammation—and diversity indices (the Shannon index, which integrates species richness and evenness, with higher values indicating greater diversity; and the Simpson index, which emphasizes the dominance of key species, with lower values indicating greater diversity). These metrics will be used to evaluate the severity of postoperative gut microbiota dysbiosis in AD patients and the regulatory effects of taVNS on the microbiota.

② Brain Function Changes:

a. BCI-Related Metrics: Electroencephalography (EEG) will be used to record brain electrical activity. Measures will include EEG rhythms (α-waves: 8–12 Hz, reflecting a state of cerebral relaxation and correlating with cognitive function; β-waves: 12–30 Hz, associated with motor preparation/execution and serving as an indicator of neuroplasticity), Event-Related Potentials (ERPs: where P300 latency reflects cognitive processing speed, and P300 amplitude reflects attention engagement), Motor-Related Potentials (MRPs: which evaluate neural signals related to motor intention), and motor imagery ability (detected via BCI, reflecting the potential for motor function recovery). Together, these measures enable real-time monitoring of taVNS-induced activation of the cerebral motor cortex.b. fNIRS-Related Metrics: This non-invasive method will measure regional cerebral blood flow (rCBF). Assessments will include cerebral metabolic activity (inferred from changes in oxyhemoglobin and deoxyhemoglobin concentrations in the prefrontal cortex and motor cortex, where reduced concentrations may indicate impaired brain function) and brain region activation patterns (evaluated through the hemodynamic responses of specific brain regions during cognitive tasks to assess prefrontal executive function and motor cortex coordination, with abnormal patterns suggesting neurological dysfunction). This approach allows for non-invasive monitoring of taVNS-mediated improvements in postoperative brain function.

#### Secondary outcome measures

3.6.2

① Inflammatory Markers: Serum IL-6 and TNF-α levels will be measured via enzyme-linked immunosorbent assay. IL-6 is a key pro-inflammatory cytokine involved in systemic inflammation, and elevated levels correlate with vascular wall damage and organ dysfunction. TNF-α induces vascular endothelial cell apoptosis and promotes inflammatory cytokine cascades, with its levels positively correlating with the severity of postoperative inflammation in AD patients. Both markers will be used to evaluate the anti-inflammatory effect of taVNS.

② Neurotransmitters: Serum levels of 5-HT and BDNF will be measured via enzyme-linked immunosorbent assay. 5-HT is a critical neurotransmitter in both the central and peripheral nervous systems, involved in mood regulation and intestinal motility; reduced levels are associated with anxiety, depression, and gastrointestinal dysfunction. BDNF promotes neuronal survival, synaptogenesis, and neuroplasticity, and is closely linked to cognitive function and neural repair; low levels indicate impaired neural regeneration. These neurotransmitters will be used to evaluate taVNS-mediated regulation of the neuroendocrine system.

③ Intestinal Function: Bowel sound frequency will be recorded by auscultating periumbilical sounds every 4 h (normal range: 4–5 times per minute; reduced frequency indicates slowed intestinal peristalsis, while hyperactivity suggests intestinal irritation). The time to first postoperative spontaneous flatus and defecation will also be recorded (delays indicate impaired intestinal function recovery and serve as a direct marker of gastrointestinal dysfunction). These parameters will be used to comprehensively assess postoperative intestinal motility and function in AD patients.

④ Scale Scores: GIDS includes five items (e.g., abdominal distension, dyschezia) and has a total score ranging from 0 to 12, with higher scores indicating more severe gastrointestinal dysfunction. It will be used to assess the severity of gastrointestinal dysfunction. The HAMA consists of 14 items with a total score of 0–56 (a score ≥7 indicates the presence of anxiety, and ≥14 indicates significant anxiety). It will assess postoperative anxiety severity. The HAMD has 17 items and a total score of 0–52 (a score ≥7 suggests possible depression, ≥14 indicates moderate depression, and ≥24 indicates severe depression). It will assess postoperative depression. The SF-36 covers eight dimensions (e.g., physical function, mental health), with higher scores indicating better quality of life. It will evaluate quality of life. The PSQI includes seven components (e.g., sleep quality, sleep latency) and has a total score of 0–21 (a score >5 indicates poor sleep quality). It will assess postoperative sleep quality.

### Safety evaluation

3.7

Throughout the study, participants' vital signs will be continuously monitored, and laboratory investigations—including complete blood count, urinalysis, coagulation profile, and hepatic/renal function—will be performed. An Adverse Event (AE) is defined as any unfavorable medical occurrence following taVNS administration, irrespective of its causal relationship to the intervention. AEs may manifest as new symptoms, signs, diseases, or laboratory abnormalities. All AEs will be actively monitored, documented in the CRF, and assessed for their nature, severity (Grades 1–4), and relationship to taVNS (definitely, probably, possibly, or unrelated).

A SAE is defined as any AE that results in death, is life-threatening, necessitates hospitalization or prolongs existing hospitalization, results in significant disability or incapacity, or is a congenital anomaly. Any SAE must be reported to the Ethics Committee of Guangdong Provincial Hospital of Traditional Chinese Medicine within 24 h, accompanied by a completed SAE report form.

### Quality control

3.8

① Standardization of Personnel and Operations: All research staff will receive standardized training and must pass competency assessments to ensure consistent execution of taVNS procedures, scale evaluations, and biospecimen collection.

② Quality Control of Equipment and Testing: Standard Operating Procedures will be strictly adhered to. taVNS devices will be calibrated weekly, with stimulation intensity set to a perceptible but non-painful level. All laboratory assays will use approved reagents, and gut microbiota analysis will be conducted by an accredited third-party laboratory. Blood and stool specimens will be stored at −80 °C within one hour post-collection under unique study identifiers.

③ Data and Monitoring Management: Source data will be entered into the CRF and verified by two independent personnel. Independent monitors will audit ≥30% of cases bi-weekly to ensure data completeness and consistency across intervention records, laboratory results, and AE documentation.

④ Graded Handling of AEs: Grade 1 AEs will be managed on-site and reported within 24 h; Grade 2 AEs will lead to temporary intervention suspension with reporting within 72 h; Grade 3+ AEs will result in immediate intervention cessation and rescue measures, with reporting to the EC within 2 h. All study documents will be archived for 5 years to ensure traceability.

